
### Eye-tracking in IVR: A biomarker for treatment response?

The application of IVR may go beyond from treatment delivery to investigation of treatment response. Recent technological advancement has enabled reliable and accurate eye-tracking in commercially available HMDs, which allows researchers to explore such applications in theoretical and clinical perspectives. Eye-tracking is a technology which captures distinct eye movement types. For example, in saccadic eye movements in which the eyes scan the visual field via successive eye movements, the eyes will fixate on a certain area of interest for 200–300 ms before moving again. Hence, eye movements such as the position, number, and duration of fixations can be traced via an eye-tracker. According to a recent review on applications of eye-tracking in VR, some of the clinical applications included diagnosis and treatment of neurodegenerative disorders, measurement on visual attention, evaluation of cognitive effort, and as well as evaluation of learning outcomes [23]. Eye-tracking can be regarded as an effective way to detect cognitive decline in people with dementia/MCI [24] As such, eye-tracking seems to be a viable means to investigate the eye movements of PwD/ people with MCI during VR-based therapy, e.g., to examine whether the participant is paying enough attention to the details of the stimuli presented. Furthermore, based on previous studies on healthy adults that the average duration of fixation and the number of revisits successfully predicted learning outcomes [23], one may question if there is a causal relationship between changes in eye movements and treatment gain in MCI population. Nevertheless, this hypothesis has rarely been investigated.

### Aims and hypotheses to be tested

The proposed study aims to investigate the potential of IVR-CST in improving the cognition of people with MCI. Three research questions have been proposed and listed as follows:

Is IVR-CST a feasible treatment for the elderly with MCI?Is IVR-CST an efficacious treatment for improving cognition in the elderly with MCI?Is IVR-CST more efficacious than conventional CST (i.e., without IVR) in improving the cognition of the elderly with MCI?Is eye-tracking data collected during therapy associated with treatment outcomes of IVR-CST?

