**Hypothesis to be tested:**

1) Whether IVR-CST is a feasible intervention for the elderly with MCI. 2) Whether IVR-CST is efficacious (and more efficacious than conventional CST) in improving cognition. 3) Whether changes in eye movements across therapy and treatment outcome are associated.

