**Outcome measures and data analysis:**

The Hong Kong Montreal Cognitive Assessment and measures on executive functions/working memory will serve as primary outcomes. The within-subject (before and after therapy) and between-subject (IVR-CST vs. conventional CST) differences will be examined. Besides, eye movements during therapy in the IVR-CST group will be collected and its correlation with primary outcomes will be studied.

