**Expected results:**

Positive changes in cognition are expected after therapy in both treatment groups, which may be maintained four weeks post-therapy.

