## Materials and methods

### Study design

An open-label, two-armed, assessor-blind, randomized controlled trial will be conducted. Randomization will be done by the principal applicant using a computer-generated random sequence. Participants will be randomly allocated to the IVR-CST or conventional CST group. The assessor will be blinded to condition allocation. Both the assessor and the participants will be reminded not to talk about issues related to treatment when they meet. The treatment protocol (version 1.0, dated March 3, 2025), which contains items from the World Health Organization Trial Registration Data Set, has been registered in ClinicalTrials.gov (NCT06838494). We will inform the funding agency, the Institutional Review Board of the Hong Kong Polytechnic University, ClinicalTrials.gov, and the publisher of the protocol of any amendments to the protocol. The experimental design is summarized in Fig 1.

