### Treatment materials and procedures

In the IVR-CST group, a total of 14 IVR-CST sessions will be carried out twice per week, with each session lasting about 45 minutes. Therapy will take place in a quiet room in the community elderly centres. A research personnel who is a healthcare professional (e.g., occupational or speech therapist) with a certified CST facilitator qualification will be the group facilitator, and three to four participants with MCI will receive IVR-CST as a group throughout the sessions. An assistant will also be present to provide help if necessary. Treatment instruments will include commercially available HMDs with eye- and hand-tracking functions available (e.g., Meta Quest Pro) for each participant. Treatment materials (i.e., content to be delivered in each themed session) will be adapted from the Chinese-translated manual of CST [11]. Materials presented via HMD will include commercially available VR games suitable for the elderly, photo-real panoramic (i.e., 360-degree) images or videos, and two- or three-dimensional animated images and photos. Use of hand controllers or hand movement will be allowed in some activities, such as physical games or manipulation of 3D objects. Similar to the original CST manual, two activities with varying levels of difficulty will be available to allow some flexibility. The major difference between the level of difficulty of the currently proposed vs. the existing manual lies in the complexity of the tasks or the use of less familiar stimuli. For example, in session 10 ‘Orientation’. The original manual suggests the use of familiar local places as stimuli for discussion; in IVR-CST, less familiar places like overseas tourist spots will be introduced. Sample themed activities are given in Table 1. Treatment procedures will follow the Chinese-translated manual of CST [12]. In the first 10 minutes, participants and the facilitator will greet and meet, and sing-along a group song or share some snacks/drinks. Reality orientation will be followed by telling the participants the time, weather, and recent news/affairs. Then the facilitator will assist the participants to wear the HMD for about 30 minutes, during which the themed activity will be conducted. All participants will be seated comfortably and at a distance far enough from one another to ensure safety during hand movement during IVR exposure. According to the IVR-CST manual, the facilitator will guide the participants to conduct a range of activities, discussions, or sharing. Material presentation will be controlled by the facilitator via a laptop. S/he will not wear an HMD so that immediate assistance to the participants can be provided. In the last five minutes, the HMD will be taken off while the facilitator will round up the session. In the conventional CST group, the same treatment activities, materials, and procedures will be used, while photos, pictures, or real objects will be presented.

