## Discussion

The current study protocol aims to investigate the feasibility and clinical efficacy of IVR-CST on people with MCI. The findings will inform us about the acceptability of VR among people with MCI, the suitability of applying VR in cognitive therapy, and its efficacy when compared to conventional therapy protocols targeting the MCI population. Feedback collected from users with MCI allows clinicians, engineers, and researchers to better understand users’ perception in using VR, which is critical for the better design of hardware/software systems and content delivery for therapeutic contexts.

There are a few limitations of the proposed study. Firstly, the small sample size would reduce the power and generalizability. Secondly, some of the therapy materials are culturally specific, e.g., photos of celebrities/places, stimuli used in word games, etc. The generalization of the findings to other cultures should be made with caution. Finally, other limitations, including MCI participants not being blinded to therapy conditions and the lack of long-term follow-up (6-month or longer), also exist. Nonetheless, the initial findings will inform us about the feasibility of IVR-CST, and the efficacy will help us decide if more sources should be devoted to scaling up the study.

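### The separate question of whether IVR-CST is efficacious can be answered only by uncontrolled before-after change, because both arms receive active CST

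*Protocol article*

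**What the plan says.** All references are to the protocol article.

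- **Aims and hypotheses to be tested** poses efficacy as a question of its own, "Is IVR-CST an efficacious treatment for improving cognition in the elderly with MCI", and then asks separately about superiority over conventional CST. The abstract's hypothesis makes the same split: "Whether IVR-CST is efficacious (and more efficacious than conventional CST) in improving cognition".
- **Study design** has two arms: "Participants will be randomly allocated to the IVR-CST or conventional CST group". Under **Treatment materials and procedures** the comparator is also active: "In the conventional CST group, the same treatment activities, materials, and procedures will be used", with photos, pictures or real objects in place of the headset.
- **Abstract, Outcome measures and data analysis**: "The within-subject (before and after therapy) and between-subject (IVR-CST vs. conventional CST) differences will be examined". **Data analysis** enters time point and condition as fixed factors, with post-hoc work on any significant main effect or interaction.
- **Abstract, Expected results**: "Positive changes in cognition are expected after therapy in both treatment groups, which may be maintained four weeks post-therapy".
- **Assessment and treatment schedule** tests everyone at weeks 1, 9 and 13.
- **Discussion** lists as limitations the sample size, culture-specific materials, unblinded participants and short follow-up. The absence of an untreated comparison is not among them. The same paragraph ends by saying that "the efficacy will help us decide if more sources should be devoted to scaling up the study".

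**The concern.** A trial of two active arms with shared content can show whether the headset version adds something. It cannot show whether either version does anything compared with no CST. Because efficacy is nevertheless asked as its own question, the only evidence left for it is change over time, which has no control.

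Scores on repeated cognitive tests can rise for reasons other than therapy. The batteries are given three times in 13 weeks, so practice is possible. Participants know their condition and receive regular group contact, so attention and expectation are possible too. If a rise in both arms, which the protocol expects, were read as an answer to the efficacy question, a non-specific gain could be reported as a treatment effect.

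**Working it through.** **Step 1. Which analysis can answer which question.**

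| Question | Contrast available | Controlled by randomisation? |
|---|---|---|
| Is IVR-CST efficacious? | Before-after change in the IVR-CST arm, or the time main effect over both arms | No |
| Is IVR-CST better than conventional CST? | Between-arm difference in change | Yes |

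A practice effect common to both arms cancels in the second row and stays in full in the first.

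**Step 2. The plan's own sample size.** Stated inputs under Participants: d = 0.40, α = 0.05, power 80%, attrition 25%, N = 66. The test is not named.
- Paired before-after t-test, two-sided: 52 participants; 52 × 1.25 = 65, close to 66.
- Group-by-time F-test with f = d/2 = 0.20, two time points and an assumed correlation of 0.5: also 52, so again 65.
- Independent two-sample t-test: 100 per arm, 200 in total before attrition. This does not reproduce 66.

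The first two cannot be told apart, so the figure of 66 does not show which contrast was meant.

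**Step 3. How often a before-after test is significant when therapy does nothing.**

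Completers: 66 / 2 = 33 per arm; 33 × 0.75 = 24.75, about 25 per arm and 50 pooled.

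The retest gain g, in SDs of the change score, is not in the documents and is an assumption, so a range is shown. The test is paired, two-sided 0.05, with noncentrality g√n and n − 1 degrees of freedom. For example, g = 0.4 with n = 25 gives 0.4 × 5 = 2.0; with n = 50 it gives 0.4 × 7.07 = 2.83.

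| Assumed gain (SD of change) | One arm, n = 25 | Pooled, n = 50 |
|---|---|---|
| 0.1 | 8% | 11% |
| 0.2 | 16% | 28% |
| 0.3 | 30% | 55% |
| 0.4 | 48% | 79% |
| 0.6 | 82% | 99% |

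The nominal rate is 5%. In a simulation with the same gain in both arms (25 per arm, 20,000 runs, assumed SD of change 2.5 points, gains of 0.5 to 2 points), the between-arm test stayed at about 5%.

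**Step 4. Power of the contrast that remains.** Two-sample t-test, d = 0.40, two-sided 0.05:
- 25 per arm: noncentrality 0.40 × √(25/2) = 1.41, power 28%.
- 33 per arm (no attrition): 36%.
- 25 per arm with baseline adjustment, effective d = 0.40 / √(1 − r²): assumed r = 0.5 gives 0.46 and power 36%; assumed r = 0.7 gives 0.56 and power 49%.

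**The case against.** An active comparator is a legitimate choice, and the comparative question is sound. That stands; the point concerns only the separate efficacy question. Blinded scoring, including of the time point, also guards against rater bias. It does not remove practice, attention or expectation.

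Four stronger readings are tempting, and the documents do not support them.

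- *The authors will declare efficacy from within-arm change.* A reader might infer this from the expected results. The text says only that differences will be examined and sets no rule for declaring efficacy from the time effect.
- *Scale-up will rest on within-arm change.* The Discussion also speaks of efficacy relative to conventional protocols, and it pairs efficacy with feasibility as initial findings. The scale-up sentence may well mean the comparative result. The text is open on this.
- *Regression to the mean will push scores up.* Entry is by a score of 16 to 21 out of 30 on the Hong Kong Brief Cognitive Test, bounded on both sides. The outcome baseline is a different test, the HK-MoCA at week 1. Bias in HK-MoCA change would need short-term error shared by the two, which the documents do not show. It is possible but secondary.
- *The false-positive rate is 48% or 79%.* Those are single points at an assumed gain of 0.4 SD. The result depends almost wholly on the assumed gain.

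Nor should the between-arm contrast be called free of bias: participants are unblinded and 25% attrition is assumed. It is the only randomised contrast, which is the accurate claim.

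**Conclusion.** The point holds in this limited form. The design cannot answer the stand-alone efficacy question, because nothing in it separates a treatment effect from practice and non-specific effects, and the limitations do not say so. No analysis model can supply the missing comparison.

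The possible size runs from slight (8% against a nominal 5%, one arm, gain 0.1 SD) to near certainty of a significant result (99%, pooled, gain 0.6 SD). These figures rest on an assumed retest gain, a zero treatment effect and 25 completers per arm; they illustrate the exposure and do not estimate the error in this trial. The superiority question is not affected by effects that the two arms share.

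**What to change.** 1. Reword the second research question and the matching abstract hypothesis. State that within-arm change is reported descriptively with a 95% CI and is not used to claim efficacy.
2. Base any efficacy conclusion on the randomised IVR-CST versus conventional CST contrast, described as added benefit over CST.
3. State in the Discussion that this contrast is the efficacy input to the scale-up decision, alongside feasibility.
4. Add the lack of an untreated arm and the repeated testing to the limitations.

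**Cost.** The changes are to wording, but the claim becomes narrower and rests on a weak contrast: about 28% power at d = 0.40 with 25 completers per arm, or about 36% to 49% with baseline adjustment at an assumed correlation of 0.5 to 0.7. The protocol should therefore say that a non-significant contrast is inconclusive and is not evidence of no added benefit. An untreated arm is not requested: at d = 0.40, comparing it with IVR-CST would need 100 completers per arm unadjusted, so 200 / 0.75 = 267 randomised for two arms.

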### Data analysis

Primary and secondary outcomes will be scored by a trained research assistant who is not involved in the assessment. To further reduce observer bias, a random code will be given to the scoring forms and audio-recording so that the research assistant will be blind to the identity of the participant, the experimental group assigned, and the timepoint of assessment. A linear fixed-effect model will be used to evaluate the participants’ performance in the outcome measures, as this statistical model is better in handling repeated observations, missing data, and individual variability [33]. Both time points (week 1/9/13) and conditions (IVR-CST vs. conventional CST) will serve as fixed factors, and scores of primary/secondary outcomes as dependent variables. Participants’ characteristics, such as age, baseline cognitive performance, and education, will be included in the model as covariates. Any significant main effects or interactions will be investigated via post-hoc analyses. Measurements concerning feasibility and user experience will be evaluated descriptively. In addition, a narrative summary of responses collected during the post-therapy interview will be reported.

For exploratory outcome, a 5-minute sample will be extracted from each participant and session from the IVR-CST group. To study possible changes in eye movement across sessions, the aforementioned eye-tracking parameters, including number of fixations, duration of fixation, and number of revisits on the AOI generated by each participant, will be evaluated by linear fixed-effect models as dependent variables, with session number as a fixed factor. Any significant main effects will be followed by post-hoc analyses. To investigate the possible associations between eye movement and treatment outcome, the correlation between the averaged difference in number and duration of eye fixations of each participant in the first and last three IVR-CST sessions and the difference score of HK-MoCA before and immediately after therapy will be analysed. If the correlation reaches statistical significance, multiple regression will be conducted, with the eye-tracking parameters as predictors, while the difference score of HK-MoCA pre/post therapy will serve as the predicted variable.

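### Research question 4 asks about eye-tracking data in general, but the planned association tests only first-to-last change, so a null result could not answer the question as worded

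*Protocol article*

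**What the plan says.** The protocol article puts the eye-tracking question in two ways.

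- **Broad.** The last question under Aims and hypotheses to be tested is "Is eye-tracking data collected during therapy associated with treatment outcomes of IVR-CST". The abstract, under Outcome measures and data analysis, likewise promises to study how eye movements during therapy correlate with the primary outcomes. Neither is limited to change.
- **Narrow.** The abstract's hypothesis is "Whether changes in eye movements across therapy and treatment outcome are associated". The Introduction section on eye-tracking also ends on change: "one may question if there is a causal relationship between changes in eye movements and treatment gain in MCI population".

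That Introduction section motivates the work with evidence about level. In healthy adults, "the average duration of fixation and the number of revisits successfully predicted learning outcomes". One use it gives for eye-tracking is "to examine whether the participant is paying enough attention to the details of the stimuli presented".

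The Data analysis section fixes the association analysis. The predictor is "the averaged difference in number and duration of eye fixations of each participant in the first and last three IVR-CST sessions". On the outcome side, "the difference score of HK-MoCA before and immediately after therapy will be analysed". Then: "If the correlation reaches statistical significance, multiple regression will be conducted, with the eye-tracking parameters as predictors". It does not say whether those predictors are levels or changes. Revisits are recorded, but they are not in the correlation. Separate models describe each eye-tracking parameter by session number and contain no outcome score. Outcome measures and procedures labels eye-tracking an exploratory outcome in the IVR-CST arm.

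**The concern.** A difference between late and early sessions removes whatever is constant within a participant. Someone who attends closely throughout and someone who hardly attends at any point both score near zero. If benefit depends on how much attention is given during therapy, which is the kind of relation the cited healthy-adult evidence describes, the planned correlation cannot show it. The regression offers no dependable second route even if its predictors are levels, because it is run only when the change correlation is significant.

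What is at stake is the conclusion. A null change correlation, reported against question 4 as worded, would read as no association between eye-tracking data and outcome. The analysis could not support that statement, although the data needed to examine level are already being extracted from every session.

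**Working it through.** **Is there a planned figure to reproduce?** No. The protocol gives no expected correlation, power or sample size for the eye-tracking association.

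**Inputs from the protocol article.** Total sample 66, allocation 1:1, attrition 25% (Participants; Randomization). The IVR-CST arm has 66 / 2 = 33, and 33 × 0.75 = 24.75, about 25 completers. There are 14 sessions. The association uses 3 + 3 = 6 of them, so sessions 4 to 11 (8 of 14, 57%) do not enter it.

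**Step 1: what the index can see.** D = mean(last three sessions) − mean(first three sessions).
- 40 fixations in every session: D = 40 − 40 = 0, session mean 40.
- 10 fixations in every session: D = 10 − 10 = 0, session mean 10.

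The session mean separates these two participants and D does not. This needs no assumption.

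**Step 2: what follows for detection.** These assumptions are illustrative and not from the documents: stable level L with SD 1; linear change C across the 14 sessions with SD 0.5; independent session noise with SD 0.5; L and C independent. Sessions are spaced evenly from −0.5 to 0.5, so the last three average 0.423 and the first three −0.423, a gap of 0.846.

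- Noise variance of D: 0.25 × (1/3 + 1/3) = 0.167. Change variance in D: (0.5 × 0.846)² = 0.179. L cancels.
- If gain correlates 0.5 with change: expected r with D = 0.5 × 0.423 / √(0.179 + 0.167) = 0.36. Expected r with the session mean = 0, because linear change averages out.
- If gain correlates 0.5 with level: expected r with D = 0. Expected r with the session mean = 0.5 / √(1 + 0.25/14) = 0.50.

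Simulation with 20,000 replicates and a two-sided 5% test agrees, apart from slight small-sample shrinkage:

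| Gain depends on | n | Planned difference: mean r, power | 14-session mean: mean r, power |
|---|---|---|---|
| Level, 0.5 | 25 | 0.00, 5% | 0.49, 74% |
| Level, 0.5 | 33 | 0.00, 5% | 0.49, 86% |
| Level, 0.6 | 25 | 0.00, 5% | 0.59, 91% |
| Level, 0.6 | 33 | 0.00, 5% | 0.59, 97% |
| Change, 0.5 | 25 | 0.355, 44% | 0.00, 5% |
| Change, 0.5 | 33 | 0.354, 55% | 0.00, 5% |

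**Range with noisier sessions.** With a single-session intraclass correlation of 0.3 to 0.7 and a level correlation of 0.5, the session mean has about 67–74% power at n = 25 and 79–86% at n = 33. With a level correlation of 0.4 it has about 46–51% and 59–64%. The planned difference stays at about 5% throughout.

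**Reading.** The two indices are complementary, and each is blind to the other's effect. The 5% figures restate the assumption that one component is unrelated to gain. They show what each analysis cannot answer, not which effect is likelier.

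**The case against.** The strongest reply is that the planned analysis matches the stated hypothesis. The abstract says changes, and the sentence that cites the level evidence goes on to ask about "one may question if there is a causal relationship between changes in eye movements and treatment gain in MCI population". Question 4 is a short general question, and methods sections often make such questions specific. A first-to-last difference is still eye-tracking data collected during therapy. Under the change hypothesis the planned index is the better one, and the session mean would do no better than chance.

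Level also has a weakness of its own. The Introduction says that eye-tracking can detect cognitive decline, so a person's mean level may partly reflect baseline severity. A within-person change removes stable differences of that kind.

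All of this stands. It rules out several stronger readings that a reader might infer:

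- **That the analysis departs from the trial's hypothesis.** It departs only from the broader wording of question 4 and of the abstract's analysis paragraph.
- **That the session mean is the more powerful choice.** That holds only if gain follows level, and the cited evidence for level concerns healthy adults, not people with MCI.
- **That leaving out sessions 4 to 11 is a fault in itself.** An early-versus-late contrast naturally omits the middle, and those sessions are analysed in the session-number models, though not against outcome.
- **That the change correlation would turn out negative under a level effect.** The calculations give about 0.00.

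The reply leaves one thing untouched: a null change correlation does not answer question 4 as it is worded.

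**Conclusion.** The point holds as a mismatch of scope. The question is asked broadly in the aims and the abstract's analysis paragraph, and narrowly in the abstract's hypothesis and the Introduction. The Data analysis section tests only the narrow version, and the regression that follows depends on the same test. That a change score carries no information on stable level is arithmetic and needs no assumption. The power figures (about 5% against 74–86% one way, 44–55% against about 5% the other) rest on illustrative variances and correlations, and the documents give nothing to choose between the two cases.

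The consequence is limited. Eye-tracking is exploratory, is collected in one arm, and enters neither the sample size nor the between-arm comparison. But question 4 is a listed research question, and as planned the trial could give it a negative answer that its analysis does not support.

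**What to change.** In Data analysis, keep the change correlation and add a second exploratory association that does not depend on any significance result. For number of fixations, duration of fixation and number of revisits, take each IVR-CST participant's mean over all recorded sessions. Relate it to the HK-MoCA change from before to immediately after therapy, with baseline HK-MoCA in the model because level may partly reflect baseline severity. Report the level and change estimates with 95% confidence intervals whether or not either is significant, and answer question 4 separately for each.

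Alternatively, if only change is of interest, reword question 4 and the matching sentence in the abstract's Outcome measures and data analysis to changes in eye movements. A null result would then be read no more widely than it should be.

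The first option uses samples already extracted for the session models. Its cost is three more exploratory estimates, one per parameter, labelled as such. The second costs a few words.
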